### Laboratory evaluations, assays, and handling

Maternal participants will be tested for Anti-ZIKV IgM antibodies using a serological assay with Emergency Use Authorization (EUA) approval from the United States Food and Drug Administration (FDA). As more specific/sensitive assays are developed, those assays may be substituted. DENV serology may be run in parallel to the Zika serology. If a routine monthly visit blood sample tests positive (ZIKV IgM and/or other serological assay), an EUA-approved ZIKV molecular assay will be performed for the detection of ZIKV RNA. Timely testing and reporting are a priority but may be limited due to laboratory capacities. All sites will use the same molecular and serological test kits and a standardized protocol.

Among maternal participants, assays to detect antibody to toxoplasma, rubella, CMV, or HSV will be run per local clinical laboratory procedures. The rapid plasma reagin (RPR) test for syphilis will be performed on plasma in accordance with local clinical laboratory procedures. Because false positives may occur, additional testing may be conducted as part of the clinical care. Assays for the detection of antibody (ELISA) or viral RNA (by RT-PCR) may be performed for DENV and in some cases for chikungunya virus (CHIKV) or WNV as appropriate per local epidemiologic disease surveillance report guidelines. Additionally, urine will be collected from maternal participants, at selected sites, to test for environmental contaminants such as phthalates, pesticides, and other chemicals.

Infant birth visit blood specimens will be evaluated by antibody assay for toxoplasma, rubella, CMV, or HSV, per local clinical laboratory procedures. The rapid plasma reagin (RPR) test will be performed on plasma in accordance with local clinical laboratory procedures. Infants will undergo diagnostic testing for ZIKV if they have clinical indication for ZIKV testing (i.e., birth defects consistent with congenital Zika syndrome or they were born to mother with laboratory evidence of possible ZIKV infection during pregnancy).

All biological samples will be received, processed, aliquoted, and stored at each site’s central laboratory. Samples may be shipped from each clinical collection site to the designated central repository for each site in each country following designated study sample shipping procedures.

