#### Secondary objectives

To determine the long-term clinical sequelae among infected infants.To determine the rate of ZIKV seroconversion among pregnant women from ZIKV-endemic regions.To compare the severity of maternal and infant outcomes by gestational age, stratified by symptomatic and asymptomatic ZIKV infection.To compare occurrence of adverse maternal and fetal outcomes (including preeclampsia, preterm birth, intrauterine growth restriction (IUGR), and oligohydramnios/polyhydramnios) between women who become infected with ZIKV infection during pregnancy and women who do not.To compare occurrence of adverse maternal and fetal outcomes (including preeclampsia, preterm birth, IUGR, and oligohydramnios/polyhydramnios) between women with symptomatic vs. asymptomatic ZIKV infection.To determine if coinfections and cofactors (including social and environmental factors) contribute to the presence and severity of CNS malformations and disease in the offspring.To determine the duration of ZIKV persistence and shedding during pregnancy in blood, urine, genital secretions, and saliva.To determine whether mothers with ZIKV infection prior to or after delivery shed virus in breast milk and to determine the incidence of postpartum infant ZIKV infection acquisition.

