Women testing positive for ZIKV will be scheduled for two additional clinic visits within 2 weeks for collection of additional blood, urine, saliva, vaginal fluid samples and a fetal ultrasound, per country and local guidelines. In addition, the MoH and local health jurisdictions will be informed per in-country regulations/requirements. Following local regulatory requirements, participants will be given their test results and counseled as needed to explain test results. Counseling may include information about the limitations in interpretation of the assays and provision of social support, as appropriate.

Infants will be assessed for ZIKV infection at birth with laboratory assessment from cord blood or peripheral blood, urine, and saliva. They will be evaluated for signs and symptoms of neurological abnormalities and will undergo auditory and visual screening. In addition, infants will be seen at 3, 6, and 12 months for a general physical exam; neurological assessment; auditory, visual, and neurodevelopmental screening assessments; and laboratory testing. If auditory, visual, or neurodevelopmental evaluations are abnormal, infants will be referred for additional testing and results recorded. Data from any radiological testing for infants with ZIKV exposure done for clinical care will be recorded. Infants noted to have any deficits will undergo appropriate follow-up and testing. If cerebrospinal fluid (CSF) is collected per clinical guidelines, remaining CSF will be stored in the study bio-repository for future testing.

See Tables 1 and 2 for additional information about data and specimen collection.

**Table 1 Tab1:** Data collection details

Assessment	Time frame	Data collected
Maternal Data		
Demographic Survey	Study entry	Basic demographics, e.g., age, race and ethnicity, marital status, and education
Medical History	Study entry	History of: significant medical disorders; previous DENV or Yellow Fever infections and vaccination; any prior infections with parvovirus, herpes, cytomegalovirus, and syphilis
Physical examination and Zika-like symptoms questionnaire	All visits	Assessment of general appearance, including height and weight, and blood pressure and temperature; history of recent symptoms consistent with ZIKV infections, including rash, fever, arthralgias, eye pain, and conjunctivitis

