Serum, plasma, whole blood, urine, saliva, vaginal swab	X	X	X	X	X	X	X
Breast milk					X	X	
Amniotic fluid (if possible)			Only if amniocentesis was performed for clinical care		X		
Cord blood (if possible)					X		
Placenta and fetal tissue if fetal loss (if possible)					X		
Infant specimen collection schedule							
	Birth	3 months		6 months			12 months
Urine, saliva, serum	X	X		X			X
Cerebrospinal fluid (remnant specimen)	Only if collected for clinical care	Only if collected for clinical care		Only if collected for clinical care			Only if collected for clinical care

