#### Sample size calculations for primary objectives

The power of the study to detect a difference was estimated by simulation, using the prevalence of ZIKV infection and adverse fetal outcome (Table 3 and Table 4). These power simulations are based on Fisher’s Exact Tests comparing the rate of adverse outcome among ZIKV infected and uninfected participants, and do not adjust for maternal covariates or differences in prevalence or outcomes among different sites or different countries, as the final analysis will do. All simulations were based on 10,000 repetitions and a two-sided unadjusted alpha level of 0.05.

**Table 3 Tab3:** Sample size to detect prevalence of primary outcomes among ZIKV infected and uninfected study participants

Proportion of pregnant women with ZIKV infection	Prevalence of congenital malformations and adverse fetal outcomes among ZIKV uninfected women	Prevalence of congenital malformations and adverse fetal outcomes among ZIKV infected women	Total number of women	Power
15%	1%	2%	6000	65%
			8000	77%
			10,000	85%
		3%	6000	98%
	2%	4%	6000	91%
20%	1%	2%	6000	74%
			8000	84%
			10,000	91%
25%			6000	80%
			8000	90%
			10,000	95%
	2%	4%	6000	97%

**Table 4 Tab4:** Sample size to detect prevalence of primary outcomes among ZIKV infected symptomatic and asymptomatic participants

Proportion of women with ZIKV symptoms	Prevalence of congenital malformations and adverse fetal outcomes among uninfected and asymptomatic women	Prevalence of congenital malformations and adverse fetal outcomes among ZIKV symptomatic women	Total number of women	Power
3%	1%	3%	6000	57%
			8000	69%
			10,000	77%
4%			6000	68%
			8000	78%
			10,000	85%
5%			6000	75%
			8000	84%
			10,000	91%
		4%	6000	94%
			8000	97%
			10,000	99%

Table 3 shows the sample size needed to detect a difference in the prevalence of ZIKV exposure in fetuses and infants of women who become infected with ZIKV compared to women who do not with 90% power, under a range of assumptions. For example, with a 25% prevalence rate of ZIKV infection among pregnant women, a 1% rate of the composite fetal outcome among uninfected women and a 2% rate of this outcome among women with ZIKV infection, we would need at least 8000 women to have 90% power to detect a difference. Assuming a 25% lost to follow-up rate in our sample, this suggests enrolling at least 10,000 women.

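### Two sections disagree on which infants are tested for ZIKV; under the restrictive rule, infection status depends on outcome for infants of test-negative mothers, which could bias secondary objectives

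*Protocol article*

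**What the plan says.** Study procedures describes the birth visit without any restriction: "Infants will be assessed for ZIKV infection at birth with laboratory assessment from cord blood or peripheral blood, urine, and saliva". It then says that "infants will be seen at 3, 6, and 12 months for a general physical exam" and other assessments. Laboratory testing is on that list, but the virus is not named.

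Laboratory evaluations, assays, and handling sets a condition: "Infants will undergo diagnostic testing for ZIKV if they have clinical indication for ZIKV testing". The indication is spelled out as "birth defects consistent with congenital Zika syndrome or they were born to mother with laboratory evidence of possible ZIKV infection during pregnancy".

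Table 2 schedules infant specimens ("Urine, saliva, serum") at birth, 3, 6 and 12 months for every infant, whatever the indication.

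Two secondary objectives need the infant's own infection status: "To determine the long-term clinical sequelae among infected infants" and "to determine the incidence of postpartum infant ZIKV infection acquisition". The second shares its sentence with breast-milk shedding by mothers infected before or after delivery. The overall aim at the end of the Background also includes the risk of vertical transmission.

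**The concern.** The two sections give different answers to a basic question: is a healthy infant of a test-negative mother tested for ZIKV at birth? No passage settles it.

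If the conditional rule is the one in force, the route to testing differs by mother. Infants of mothers laboratory-positive in pregnancy are tested whatever their outcome. Infants of test-negative mothers are tested only if they already have a defect. If maternal surveillance misses an infection, the affected infant can enter the group of infected infants and the unaffected one cannot. A proportion with sequelae in that mixed group is then partly fixed by how its members were found.

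The same rule leaves a gap for acquisition after birth. Its maternal trigger is infection during pregnancy, so an infant whose mother is infected only after delivery does not qualify unless it has a birth defect, although the objective names such mothers.

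**Working it through.** The plan states no figure on infant testing, so there is none to reproduce. The planning rates come from Sample size calculations for primary objectives. As a check that they are read correctly, the worked-example cell of Table 3 (25% infected, 1% against 2%, 8,000 women) was re-simulated with Fisher's exact test and 10,000 repetitions. It gave 90.1% power against the stated 90%.

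**Step 1: share of infants not tested under the conditional rule.** Let p be the proportion of mothers infected (15%, 20% or 25% in Table 3; the worked example is "with a 25% prevalence rate of ZIKV infection among pregnant women"). Let d0 be the outcome rate in uninfected mothers (1% or 2%), standing in for the defect trigger.

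Untested share = (1 − p) × (1 − d0)

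| p | d0 = 1% | d0 = 2% |
|---|---|---|
| 15% | 0.85 × 0.99 = 84.2% | 0.85 × 0.98 = 83.3% |
| 20% | 0.80 × 0.99 = 79.2% | 0.80 × 0.98 = 78.4% |
| 25% | 0.75 × 0.99 = 74.3% | 0.75 × 0.98 = 73.5% |

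Table 3 has no row for 20% with 2%; that cell only completes the grid. The figures are approximate because d0 is the rate of the whole composite, which includes fetal demise and neonatal death. With a trigger rate near zero the share tends to 1 − p, that is 75% to 85%, so the result hardly depends on d0.

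**Step 2: effect on sequelae among infants classed as infected.** Let d be the true proportion affected among infected infants, and s the share of infected infants whose mother was laboratory-positive in pregnancy. The documents give neither, so both are assumptions. Infants of detected mothers contribute s to the denominator. Those of missed mothers contribute only their affected members, (1 − s) × d. All affected infants, s × d + (1 − s) × d = d, are in the numerator.

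Observed proportion = d / (s + (1 − s) × d)

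For d = 10%:

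- s = 1.0: 0.10 / 1.00 = 10.0%, no inflation
- s = 0.9: 0.10 / (0.90 + 0.01) = 11.0%
- s = 0.8: 0.10 / (0.80 + 0.02) = 12.2%
- s = 0.5: 0.10 / (0.50 + 0.05) = 18.2%, an extreme case

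The formula assumes accurate infant assays, the same d for infants of detected and missed mothers, and that every affected infant shows a triggering defect. If some sequelae appear later without such a defect, fewer infants of missed mothers enter and the inflation is smaller. If all infants are tested, the observed proportion equals d.

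**The case against.** The strongest reply is that the sections describe different things: Study procedures lists visits and specimens, and the laboratory section says which assays are run. Collecting from everyone and assaying conditionally is a pattern in this study; interim maternal urine and the molecular assay on routine monthly samples both wait for a positive serology. At 3, 6 and 12 months the text promises laboratory testing, not ZIKV testing, so only the birth sentence conflicts directly. That last point stands. But the birth sentence speaks of assessing infants for ZIKV infection, and if it does mean collection only, the conditional rule operates and its consequences follow. The full protocol may settle the wording; the article does not.

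It can also be said that women are tested monthly and whenever symptomatic, so few infections may be missed. That is fair, and it is why the range starts at no inflation. Misses remain possible: enrolment runs to 17 weeks and 6 days, so an infection can precede the first sample.

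A reader might infer a much larger distortion. For example, take 250 infected infants of positive mothers, 25 of them affected, and add 20 found through defects: (25 + 20) / (250 + 20) = 16.7% instead of 10%. At 10% affected, those 20 imply 200 infected infants of missed mothers, so 200 / 450 = 44% of infected infants would have undetected mothers. Nothing in the documents supports that.

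A reader might also infer that postpartum acquisition fails for most infants. That assumes the objective covers all infants, whereas its sentence can be read as centred on infants of infected mothers. The firm gap is the narrower one: infants of mothers infected only after delivery.

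**Conclusion.** The point holds for secondary objectives. The birth-visit sentence and the conditional testing rule conflict and must be reconciled. Under the conditional rule, sequelae among infected infants are biased upward whenever maternal infections are missed. The direction is clear, but the documents do not fix the size: nil with complete maternal detection and, on an assumed true 10%, about one to two percentage points at 90% to 80% detection. Roughly 74% to 84% of infants would have no ZIKV result, mostly because that is the planned share of uninfected mothers.

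It would be wrong to conclude that the primary comparison is compromised. It classifies by maternal infection or symptoms, not by infant infection. Nor does this rule bias vertical transmission among detected maternal infections, since all those infants qualify for testing.

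**What to change.** 1. Reconcile Study procedures with Laboratory evaluations, assays, and handling: state which infants are assayed for ZIKV at birth, and whether the laboratory testing at 3, 6 and 12 months includes ZIKV.
2. If testing stays conditional, restrict analyses of vertical transmission and of sequelae among infected infants to infants of mothers laboratory-positive in pregnancy. Report infants tested only because of a defect separately, outside those denominators.
3. For postpartum acquisition, either state that the estimate covers only infants eligible under the conditional rule, or assay the scheduled 3-, 6- and 12-month specimens of infants of mothers infected after delivery and of a random sample of infants of negative mothers. Maternal sampling ends at the 6-week visit, so later maternal infections would not be identified; only the random sample could reach those infants.

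Items 1 and 2 cost a protocol clarification, an analysis-set definition and a narrower claim. The second option in item 3 adds a modest assay cost but no new visits or sampling, because Table 2 already schedules the specimens.

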### Statistical considerations

#### Study outcome measures

The primary composite endpoint is defined as the occurrence of congenital malformations and adverse fetal and neonatal outcomes. This includes microcephaly, fetal demise, neonatal death (within first 28 days of life), CNS malformations, hydrops, ocular and hearing abnormalities, infant seizures and arthrogryposis.

#### Sample size considerations

Recruitment will target enrolling 10,000 pregnant women, in their first or early second trimester of gestation, or women with confirmed acute ZIKV infection at any gestational age, across ten sites. If either the enrollment or infection rate is significantly different from what has been projected, consideration will be given to reducing the sample size, expanding the study to include a larger sample size, adding an additional site, or focusing recruitment on ZIKV-symptomatic women or women in an area where the current incidence rate is high.

#### Sample size calculations for primary objectives

The power of the study to detect a difference was estimated by simulation, using the prevalence of ZIKV infection and adverse fetal outcome (Table 3 and Table 4). These power simulations are based on Fisher’s Exact Tests comparing the rate of adverse outcome among ZIKV infected and uninfected participants, and do not adjust for maternal covariates or differences in prevalence or outcomes among different sites or different countries, as the final analysis will do. All simulations were based on 10,000 repetitions and a two-sided unadjusted alpha level of 0.05.

**Table 3 Tab3:** Sample size to detect prevalence of primary outcomes among ZIKV infected and uninfected study participants

Proportion of pregnant women with ZIKV infection	Prevalence of congenital malformations and adverse fetal outcomes among ZIKV uninfected women	Prevalence of congenital malformations and adverse fetal outcomes among ZIKV infected women	Total number of women	Power
15%	1%	2%	6000	65%
			8000	77%
			10,000	85%
		3%	6000	98%
	2%	4%	6000	91%
20%	1%	2%	6000	74%
			8000	84%
			10,000	91%
25%			6000	80%
			8000	90%
			10,000	95%
	2%	4%	6000	97%

**Table 4 Tab4:** Sample size to detect prevalence of primary outcomes among ZIKV infected symptomatic and asymptomatic participants

Proportion of women with ZIKV symptoms	Prevalence of congenital malformations and adverse fetal outcomes among uninfected and asymptomatic women	Prevalence of congenital malformations and adverse fetal outcomes among ZIKV symptomatic women	Total number of women	Power
3%	1%	3%	6000	57%
			8000	69%
			10,000	77%
4%			6000	68%
			8000	78%
			10,000	85%
5%			6000	75%
			8000	84%
			10,000	91%
		4%	6000	94%
			8000	97%
			10,000	99%

Table 3 shows the sample size needed to detect a difference in the prevalence of ZIKV exposure in fetuses and infants of women who become infected with ZIKV compared to women who do not with 90% power, under a range of assumptions. For example, with a 25% prevalence rate of ZIKV infection among pregnant women, a 1% rate of the composite fetal outcome among uninfected women and a 2% rate of this outcome among women with ZIKV infection, we would need at least 8000 women to have 90% power to detect a difference. Assuming a 25% lost to follow-up rate in our sample, this suggests enrolling at least 10,000 women.

Table 4 shows the power of the study to detect a difference in the incidence of congenital malformations and adverse fetal outcomes in fetuses and infants of women who become symptomatic with ZIKV infection compared to women who do not, under a range of assumptions.

A key secondary objective is the association between gestational age at time of ZIKV infection and risk of adverse fetal outcome. With 10,000 women enrolled, if we assume that ZIKV exposure will be approximately uniformly distributed across trimesters and 25% of women become ZIKV positive, we would expect 800–900 women to be infected during their first trimester. If the rate of the composite endpoint among these first-trimester infections was 3%, compared to 1% in those without ZIKV infection, we would have high (> 95%) power to detect a difference. We would also have reasonable power to detect a difference between these first trimester infections and a similar number of infections at later trimesters if the increased risk is limited to the first trimester, if the trimester of ZIKV infection can be confirmed in a large enough group of ZIKV-infected women.

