To date, most studies have included only symptomatic women. A report of 88 pregnant women with a rash in Rio de Janeiro revealed that 82% tested positive for ZIKV in blood or urine. In addition to rash, women had arthralgias, conjunctival injection, and headache [30]. Twenty-nine percent of ZIKV-positive women had abnormal ultrasounds with corresponding adverse outcome of pregnancies (fetal demise or newborns with confirmed pathology). A cohort study of pregnant women with rash in Rio de Janeiro, Brazil, reported the findings of 134 ZIKV-positive women and 73 ZIKV-negative women [11]. Among 125 ZIKV-positive women for whom outcomes of pregnancy were available, adverse pregnancy outcomes were observed in 46.4%, and among 117 live-born infants, 42% had abnormalities on clinical examination, imaging, or both; 3.4% had microcephaly. Thus, self-limited symptomatic infections during pregnancy were associated with severe outcomes in the fetus. Information is limited about the incidence of fetal abnormalities among women who have asymptomatic ZIKV infection during their pregnancy. In the USZPR study, birth defects were reported in similar proportions of fetuses/infants whose mothers did and did not report symptoms [19]. Other studies have not been able to capture data on asymptomatic women.

Increasing evidence points to ZIKV as the agent responsible for a variety of birth defects in newborns of mothers who become infected during pregnancy [16, 31, 32]. However, the strength of the causal relationship of ZIKV infections in pregnancy with adverse outcomes has yet to be determined. Most studies to date have followed women known to be infected or infants who were born with serious birth defects. Previous studies have not been able to determine differences in risk of ZIKV-associated outcomes by trimester of infection, the rate of vertical transmission and factors that affect this rate, and the full spectrum of infant health outcomes associated with congenital ZIKV exposure.

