### Study objectives

#### Primary objectives

To compare the occurrence of congenital malformations and adverse outcomes (including microcephaly, fetal demise, neonatal death, CNS malformations, hydrops, and ocular abnormalities) in fetuses/infants of women who become infected with ZIKV during pregnancy compared to women who do not.To compare the occurrence of congenital malformations and adverse outcomes in fetuses/infants of women who become symptomatic with ZIKV infection during pregnancy versus those who do not.

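### Table 4's title and its comparator column describe different contrasts, and the pooled 1% reference rate conflicts with the 25% infected, 2% event-rate basis used to size the study

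*Protocol article*

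**What the plan says.** All references are to the Protocol article.

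- **Primary objectives**, second objective: outcomes are compared in fetuses and infants of "women who become symptomatic with ZIKV infection during pregnancy versus those who do not". Read literally, the reference is every woman without symptomatic infection, infected or not.
- **Sample size calculations for primary objectives**, Table 4 title: "Sample size to detect prevalence of primary outcomes among ZIKV infected symptomatic and asymptomatic participants". This names a contrast within infected women.
- Same table, reference column: "Prevalence of congenital malformations and adverse fetal outcomes among uninfected and asymptomatic women", at 1% in every row. The exposed group is 3%, 4% or 5% of all women (column "Proportion of women with ZIKV symptoms"), with a 3% or 4% event rate.
- The paragraph that describes Table 4 repeats the objective's contrast, women who become symptomatic against those who do not.
- The method statement covering both tables mentions only "Fisher’s Exact Tests comparing the rate of adverse outcome among ZIKV infected and uninfected participants".
- The worked example under Table 3, which leads to 10,000 women, takes 25% infected, 1% events in uninfected women and 2% in infected women.
- **Analyses**: the primary model uses a symptom-related indicator but names no reference group for it.
- **Secondary objectives**: for other outcomes (preeclampsia, preterm birth and similar) the plan does specify a contrast "between women with symptomatic vs. asymptomatic ZIKV infection".

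**The concern.** Two things are at stake.

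The first is what the second primary result will mean. A reference of all non-symptomatic women is mostly uninfected. A raised risk in symptomatic women against that reference can come from being infected, from having symptoms, or from both. The Background gives a reason to care: it cites a registry in which "birth defects were reported in similar proportions of fetuses/infants whose mothers did and did not report symptoms".

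The second is whether the two power tables can be true of one cohort. Table 3 gives infected women as a group twice the uninfected risk. Table 4 gives asymptomatic infected women, the majority of infected women in most of the scenarios considered, no excess risk at all.

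**Working it through.** **Inputs.** Two-sided Fisher's exact test; the article says "All simulations were based on 10,000 repetitions and a two-sided unadjusted alpha level of 0.05". I computed power by exact enumeration, with n1 = symptomatic share × N. Event rates and shares are those of Tables 3 and 4.

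**Step 1. Reproduce Table 4 (reference = all remaining women at 1%, N = 10,000).**

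| Symptomatic share, rate | Groups | Computed | Stated |
|---|---|---|---|
| 3%, 3% | 300 vs 9,700 | 77.5% | 77% |
| 4%, 3% | 400 vs 9,600 | 84.6% | 85% |
| 5%, 3% | 500 vs 9,500 | 90.8% | 91% |
| 5%, 4% | 500 vs 9,500 | 99.2% | 99% |

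Using asymptomatic infected women only, at 25% infected and still at 1% (500 vs 2,000), gives 85% for the third row, not 91%. The calculation is therefore pooled and the title does not describe it.

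**Step 2. Compare with Table 3's basis (25% infected at 2%).** With 5% symptomatic and 20% asymptomatic infected at 1%:
- symptomatic rate needed = (0.25×2% − 0.20×1%)/0.05 = 6%; Table 4 assumes 3% or 4%.
- conversely, a 3% symptomatic rate implies an infected rate of (0.05×3% + 0.20×1%)/0.25 = 1.4%; a 4% rate implies 1.6%. Neither is 2%.

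Table 3's 1%-versus-2% rows use infection shares of 15%, 20% and 25%. Pairing these with Table 4's four symptom scenarios gives 12 combinations. Only one is coherent, 15% infected with 5% symptomatic at 4%: (0.05×4% + 0.10×1%)/0.15 = 2.0%.

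**Step 3. Recompute with rates consistent with 25% infected at 2% (N = 10,000).**

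Asymptomatic rate pa = (0.25×2% − s×ps)/(0.25 − s), where s and ps are the symptomatic share and rate. Pooled reference = (0.75×1% + (0.25 − s)×pa)/(1 − s).

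For s = 5%, ps = 3%: pa = (0.50% − 0.15%)/0.20 = 1.75%; pooled = (0.75% + 0.35%)/0.95 = 1.158%.

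For s = 5%, ps = 4%: pa = (0.50% − 0.20%)/0.20 = 1.50%; pooled = (0.75% + 0.30%)/0.95 = 1.105%.

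| s, ps | pa | Stated | Pooled reference | Asymptomatic infected only |
|---|---|---|---|---|
| 3%, 3% | 1.86% | 77% | 64% | 25% |
| 4%, 3% | 1.81% | 85% | 77% | 32% |
| 5%, 3% | 1.75% | 91% | 84% | 39% |
| 5%, 4% | 1.50% | 99% | 98.7% | 88% |

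**Step 4. What the pooled contrast shows when symptoms do nothing.** Let all infected women be at 2%, uninfected at 1%, with 25% infected and 5% symptomatic. Uninfected women are 75 of the 95 parts of the reference, whose rate is (0.75×1% + 0.20×2%)/0.95 = 1.21%. The risk ratio is 2%/1.21% = 1.65. With 500 vs 9,500 women, the test is significant in 31% of studies. Across infection shares of 15% to 25% and symptomatic shares of 3% and 5%, the range is 21% to 39%.

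**The case against.** The strongest reply is that the plan is mostly consistent. Objective 2, the Table 4 column, the paragraph describing Table 4 and the fetal-loss comparison in Analyses all read as symptomatic infection against everyone else, and the calculation matches them. On that view the title is a slip. The secondary objective on symptomatic versus asymptomatic infection concerns other outcomes and contradicts nothing. This stands, and it limits the contradiction to the title. It does not remove the conflict of rates or the mixing of infection with symptoms.

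A second reply is that the tables are separate grids over ranges of assumptions, and Table 4 states no infection share. This stands in part: one pairing is coherent. But every Table 4 scenario conflicts with the 25%/2% example that the article uses to reach 10,000.

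Four stronger readings are tempting and are not supported:

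- *The second primary is uninterpretable.* Symptomatic infection against all other women is an interpretable, diluted association. Objective 2 does not claim to isolate symptoms within infected women.
- *True power is 39%.* That figure holds only on the title's reading and at a 3% symptomatic rate. At 4% it is 88%.
- *Power after dropout is 74%, not 91%.* At 7,500 women (10,000 less 25%), consistent rates give 74%, but Table 4's own inputs give 82% there. About half of that gap is loss to follow-up, a separate matter.
- *Table 3 is undermined.* Putting the implied 1.4% into Table 3 at 25% infected and 10,000 women gives 36% instead of 95%. The article never states 1.4%, so this illustrates the inconsistency and is not an error in Table 3.

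The Background's registry finding is also a single report on birth defects, in a paragraph that calls information on asymptomatic infection limited. It makes the no-symptom-effect case plausible but does not fix the asymptomatic rate.

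**Conclusion.** The point holds in a bounded form. Table 4's title and its calculation name different comparators. The pooled 1% cannot be reconciled with 25% infected at 2%. If pooling is kept and the rates are made consistent with that basis, the overstatement at 10,000 women runs from almost nothing (5% symptomatic at 4%) to about 13 points (3% symptomatic at 3%: 77% to 64%). If the contrast is the one in the title, the shortfall is much larger at a 3% symptomatic rate and about 11 points at 4%.

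The more lasting issue is meaning: on the pooled contrast, an infection effect alone produces a risk ratio of 1.65 and a significant result in 31% of studies. That follows only if the pooled comparator is used in the analysis. Objective 2 and the Table 4 text point that way, and Analyses does not exclude it.

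The recomputed figures assume that Table 3's 2% covers symptomatic and asymptomatic infected women together, as its column label indicates. They use the article's unadjusted Fisher test, not the adjusted final model.

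**What to change.** 1. Use one three-level exposure: uninfected, infected asymptomatic, infected symptomatic. Name symptomatic versus asymptomatic infected as the symptom contrast and report symptomatic versus uninfected alongside it.
2. State the comparator identically in objective 2, the Table 4 title and column, the paragraph describing Table 4, and Analyses. Extend the Fisher-test sentence to cover this contrast.
3. Recompute Table 4 with the infection share and the asymptomatic-infected rate as explicit inputs that agree with Table 3.

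The cost is wording and a rerun of one power table; no data collection changes. The stated power for the symptom contrast will fall, and the plan should say so. The recruitment target is unaffected because it is derived from Table 3. The choice should be fixed before analysis, since choosing between two comparators afterwards could be driven by the results.
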